### Participants and recruitment

Teachers from schools in the USA will be recruited to participate. Inclusion criteria include being a teacher at an elementary (typically K–5th grade or K–8th) school and not having been trained or supervised in delivering PGD in the past 5 years. We will recruit approximately 276 teachers from 46 elementary schools in the USA. The final balance of teachers and schools is dependent on recruitment, with the goal of meeting minimum statistical power. Schools will be approached to participate via multiple routes, including leveraging existing relationships and networks, educational listservs, and posting on social media. Interested school representatives may respond using the interest survey linked in flyers or by contacting the research team via email. The generalizer (generalizer.org), a free, web-based tool for selecting schools for randomized controlled designs that are statistically representative of a chosen inference population, will also be used to help assure the representativeness of our sample [58]. Strata will be created on urbanicity, school race/ethnicity, school percent female, school percent free and reduced lunch, school size, school percentage English language learners, and the number of schools in the district.

Once schools have been selected, teacher recruitment will proceed for both cohorts of schools with the assistance of site administrators. Principals will provide us with the email addresses of teachers in their schools. Research staff or school leadership will contact eligible participants by email or phone to describe the purpose of the study, research procedures, and incentives. Informed consent will be collected online prior to training (Additional file 3) and teachers will be free to decline participation. Monetary incentives will be provided to participating teachers and schools.

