##### BASIS-T structure

BASIS-T is delivered in a group-based format shortly before and after receiving EBPP (e.g., PGD) training. BASIS-T will be delivered via tele-facilitation (via Zoom or another similar video conferencing platform), pre-recorded video content, and electronic sharing of documents to promote scalability. BASIS-T facilitators are experienced school-based professionals. A *pre-training session* (75 min) targets attitudes, social norms, and perceived behavioral control. The pre-training opens with the facilitator engaging teachers in an activity to clarify their professional values (an MI component). The facilitator uses open-ended questions to elicit change talk and reflects, summarizes, and draws themes across participant responses. The pre-training session is designed to help participants (a) explore their professional values and goals and make connections between those and EBPP training opportunities, (b) link EBPP delivery to improved outcomes for students, and (c) recognize common cognitive shortcuts that leave individuals vulnerable to adopting non-EBPPs. Teachers collaboratively develop an individualized menu of potential solutions to implementation barriers from which they can select when encountering challenges and set value-congruent goals related to the upcoming EBPP training.

The BASIS-T *post-training session* (75 min) provides protected time and a structured experience to develop action plans and problem-solving plans. Teachers will be provided with an action planning template to detail what PGD components they will use, how, with whom, where/when, and the environmental cues and resources needed to serve as prompts to deliver PGD with fidelity. The problem-solving plan involves teachers anticipating situational barriers and generating solutions to overcome those barriers to develop personalized “if–then” plans for dealing with specific barriers. Teachers share their plans with colleagues to receive input and feedback and to publicly set values-based goals for implementation.

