#### Quantitative surveys

Participants will complete secure web-based surveys at 13 timepoints spanning three phases: preparation (times 1–4), active implementation (times 5–11), and sustainment (times 12–13 follow-up during the next academic year) [45]. Time 1 will occur during informed consent, time 2 in the days immediately before BASIS-T/ACC pre-training, time 3 immediately after pre-training, time 4 immediately after post-training, time 5 two weeks after training, time 6 four weeks after training, times 7–11 monthly until the end of the academic year, time 12 at the beginning of the subsequent academic year, and time 13 during the spring of that academic year. Teachers will self-report demographics, perceptions about BASIS-T (when relevant) and PGD training, BASIS-T mechanisms, implementation outcomes, organizational moderators (implementation climate, leadership), and time and resources used for PGD implementation. From times 7–11, to reduce the respondent burden we will use a random item planned missingness design for measures of attitudes (1 item selected per subscale), action self-efficacy (2 items selected), and subjective norms (1 item selected per each scale).

Data collection regarding students will focus on classroom behavior, behavioral discipline, attendance, and academic performance and will be collected in aggregate at the classroom level, without individual identifiers. Teachers will complete the first secure online survey on student classroom behavior at time 4, as earlier data collection would prohibit teachers from having an adequate sample of student behavior. At the end of each school year, academic and behavioral data (attendance, disciplinary actions, grades, and standardized test scores) will be requested for all students who were in classrooms of participating teachers; these data will be obtained in aggregate at the classroom level and no individual identifiers will be provided to the research team.

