We will use thegeneralizer.org to compare our sample to national demographics to examine the generalizability of our findings [58]. If not generalizable, we will use inverse probability weighting to increase the representativeness of estimates [87].*RQ 1a*: A series of 3-level piecewise mixed effects models will be used to test our primary hypotheses: (1) the BASIS-T condition will show steeper gains than the ACC condition from T1 to T2 (e.g., more favorable attitudes towards EBPPs, increased social norms; enhanced task and maintenance self-efficacy; stronger intentions to implement) and (2) both groups will decline after training (T3–T5) as has been found in past TPB research [88], and in the BASIS-T pilot trial [33], but the BASIS-T condition will have longer sustained between-condition effects after training from T3 to T13. Dependent variables will include subscale scores on attitudes, social norms, self-efficacy, intentions, and maintenance self-efficacy.*RQ 1b*: BASIS-T impact on behavioral implementation outcomes will be tested in two ways. First, a mixed effects model will examine whether the proportion of teachers in the BASIS-T condition who adopt PGD (i.e., initiate PGD) is higher than the proportion in the ACC condition. Second, Kaplan–Meier time-to-event analyses will be used to compare conditions on the number of days between training and PGD initiation. Reach will be analyzed using mixed effects models comparing BASIS-T vs. ACC on the proportion of students in each classroom (out of those eligible based on whether their classroom teacher participated in PGD training) who received PGD practices. Impact on PGD fidelity will be analyzed using mixed effects models with sessions within teachers, testing for the main effects of condition on adherence and participant responsiveness ratings derived from both PGD observational and self-report fidelity data. We will test the effects of BASIS-T on PGD sustainment and delayed implementation using the multilevel longitudinal analytic approach described for RQ1a.*RQ1c*: BASIS-T impact on student SEB and academic outcomes will be tested via mixed effects multilevel models as described in RQ1a, with academic data aggregated to the classroom level. Dependent variables will include post-intervention scores on teacher ratings of student behavior.*RQ2a*: Whether mechanisms of behavior change mediate the impact of BASIS-T on implementation outcomes will be analyzed using path analysis [89] extending traditional mediation modeling to a multi-level framework for nested data [90, 91].*RQ2b*: To test whether the effect of BASIS-T on implementation and student outcomes is moderated by teacher factors (e.g., demographics, baseline intentions to implement) and school-level factors, we will add moderators and interaction terms to the analytic approach described in RQs 1a-c.*RQ2c*: To explore what explains “residual” teachers whose implementation behaviors are not accounted for by the mediation model, we will analyze qualitative interviews with teachers who have a difference between predicted (based on BASIS-T putative mechanisms) and actual implementation behavior of ≥ 1 SD. Data will be coded using an integrated directed and conventional content analysis [92] approach as certain codes will be conceptualized during the interview guide development and driven by the exploration, preparation, implementation, sustainment [93] framework (i.e., deductive approach) which will allow for the examination of influences on implementation across multiple levels and phases. Other codes will be developed through a close reading of an initial subset of transcripts (i.e., inductive approach). These themes will provide a way of identifying and understanding the most salient factors that impact implementation and extend beyond the existing BASIS-T mechanisms and theory of change. After a stable set of codes is developed, a consensus process will be used in which all reviewers independently code and compare their coding to arrive at consensus judgments through open dialogue [78, 79, 94].*RQ2d*: We will process cost data by assigning monetary values to each cost. We will use CostOut [95], a web-based program for conducting cost-effectiveness analysis in education, to identify nationally representative unit prices for ingredients. For qualitative data, we will rapidly analyze responses on an ongoing basis [96, 97] and incorporate newly identified costs into future surveys for quantitative measurement.

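### The wave labels in the RQ 1a primary hypotheses contradict the survey schedule and the piecewise segments: T1 to T2 holds no exposure, and T3 to T5 is not wholly after training

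*Protocol article*

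**What the plan says.** All references are to the Protocol article.

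The Data analytic plan, under RQ 1a, names two primary hypotheses. The first is that "the BASIS-T condition will show steeper gains than the ACC condition from T1 to T2", with attitudes, norms, task and maintenance self-efficacy, and intentions given as examples. The second begins "both groups will decline after training (T3–T5" and adds that the between-condition effect will be sustained for longer in BASIS-T from T3 to T13.

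The schedule is under Quantitative surveys: "Time 1 will occur during informed consent, time 2 in the days immediately before BASIS-T/ACC pre-training", then "time 3 immediately after pre-training, time 4 immediately after post-training". T5 and T6 follow two and four weeks after training, T7–T11 are monthly, and T12–T13 fall in the next school year. Participants and recruitment agrees on the order: "Informed consent will be collected online prior to training".

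BASIS-T structure fixes when exposure starts: "BASIS-T is delivered in a group-based format shortly before and after receiving EBPP (e.g., PGD) training". The post-training session "provides protected time and a structured experience to develop action plans and problem-solving plans".

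The general part of the Data analytic plan defines four piecewise segments: T1–T4 (labelled as training), T5–T6, T7–T11 and T12–T13. It tests group differences in slope and in level at the last wave of each segment, at p < 0.05.

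**The concern.** A primary hypothesis should name a window in which the strategy can act. Hypothesis 1 names one in which nothing has been delivered to either arm. An analyst who followed the sentence literally would test a pre-exposure contrast. A significant result there would reflect chance or imbalance but could be reported as an effect of BASIS-T, and a null result would say nothing about BASIS-T.

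Hypothesis 2 has a related fault. Its window starts after the pre-training session only, so it takes in PGD training and the second BASIS-T session before any true post-training period begins.

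The model segments give a different window for hypothesis 1 from the one in the hypothesis itself, and nothing says which governs. If this is left open, the window for the primary question could be chosen after the data are seen. The planned false discovery rate adjustment covers multiple dependent variables, not a choice of window.

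**Working it through.** The plan gives no figure to reproduce on this point. The check is to set the windows against the schedule.

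**Order of events** (Quantitative surveys; BASIS-T structure)

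1. T1: consent
2. T2: days before the pre-training session
3. BASIS-T or ACC pre-training session
4. T3
5. PGD training, then the BASIS-T or ACC post-training session
6. T4
7. T5 (two weeks after training), T6 (four weeks), and onward

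**What each window contains**

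| Window | Source | Condition-specific content inside it |
|---|---|---|
| T1–T2 | hypothesis 1 | none |
| T1–T4 | first model segment | both sessions |
| T3–T5 | hypothesis 2, decline | post-training session, plus PGD training in both arms |
| T3–T13 | hypothesis 2, sustained effect | starts after the first session, before the second |

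**T1–T2 contrast.** No condition-specific content is delivered, and the Randomization section has participants masked, so no expectancy difference is planned either. Under randomisation the expected arm difference in change is 0. The chance of rejection is then 0.05 at any sample size. With a two-sided test, half of that, 0.025, falls in the favourable direction. The document does not state sidedness.

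**Scale of the contrast (illustration).** Take the Power section's 46 schools, 6 teachers per school and ICC of 0.10. For a standardised two-arm comparison without covariates:

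SE = √(4 × 0.10/46 + 4 × 0.90/(46 × 6)) = √(0.00870 + 0.01304) = 0.147

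At a true d of 0.37 the non-centrality is 0.37/0.1474 = 2.51 on 44 df. The rejection probability is 0.69 two-sided or 0.80 one-sided. Over T1–T2 it stays at 0.05, because the true difference there is 0. This is a single-contrast approximation, not the fitted piecewise model.

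**T1–T4 slope.** Code the four waves 0, 1, 2, 3 (equal spacing is an assumption). The mean is 1.5 and the sum of squared deviations is 5.

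- Effect d present at T3 and T4: slope = (0.5 + 1.5)d/5 = 0.4d per step. Fitted T4 difference = 0.5d + 1.5 × 0.4d = 1.1d.
- Effect d present at T4 only: slope = 1.5d/5 = 0.3d per step. Fitted T4 difference = 0.25d + 1.5 × 0.3d = 0.7d.

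The fitted segment therefore carries an effect in either case, where T1–T2 carries none.

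**T3–T5 change.** This is the sum of the T3–T4 change (over training) and the T4–T5 change (after training). If the first is a gain and the second a loss, they partly or wholly cancel. No T3–T4 change is given for any mechanism, so the amount cannot be computed. No fitted slope matches T3–T5 either, since it runs across the break between the first and second segments.

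**Could it be an offset in numbering?** Moving every label up by one gives T2–T3 for the gain and T4–T6 for the decline, both of which fit the schedule better. But T13 would become T14, and there are only 13 waves. The shifted hypothesis 1 would also stop before the post-training session, although it lists maintenance self-efficacy, which Table 1 ties to action and problem-solving planning.

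**The case against.** The strongest reply is that the plan never fits a T1–T2 slope. RQ 1a says that piecewise models test the hypotheses, and those models use T1–T4 and a comparison at T4. This stands. A reader might infer that the primary analysis has power equal to alpha and cannot succeed. The document does not support that: the statement holds only for a literal T1–T2 contrast.

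Second, the intended meaning (a gain over training, then a decline) is fairly clear, and the labels look like a slip. That is plausible, but the document does not say so and a uniform shift does not repair it.

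Third, two stronger claims about hypothesis 2 and its mechanisms are tempting and go too far:

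- A reader might infer that the decline will be cancelled by a training gain. The document shows only that it could be. Both arms receive PGD training (Intervention), so that part need not bias the comparison between arms. For the motivational mechanisms T3 is already after exposure, so an effect from T3 to T13 is not an empty window.
- A reader might infer that maintenance self-efficacy is targeted only after training. Table 1 places it with the volitional components, but the pre-training session also has teachers build a menu of solutions to barriers. It is addressed mainly, not solely, in the later session.

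Finally, the zero expectation rests on randomisation. The Randomization section allows some allocation by trainer availability, so an exact 5% is not assured.

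**Conclusion.** The contradiction is real and sits in the declared primary hypotheses. Hypothesis 1 names a window with no exposure. Its expected arm difference is 0, and its rejection rate is 0.05 if allocation is random and nothing condition-specific reaches teachers before the pre-training session. The specified model uses a different window, T1–T4, that can detect an effect. The fault is therefore two incompatible windows for one primary question. It is not a design that is unable to answer that question, and the data remain usable.

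Hypothesis 2 mislabels T3–T5 as after training. A decline could be masked there, by an amount the document does not allow one to compute.

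Neither conclusion depends on a sample size figure. The 0.4d, 0.3d, 1.1d and 0.7d values assume equally spaced waves and the stated step patterns.

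**What to change.** Align RQ 1a with the survey schedule and the model segments:

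- **Hypothesis 1:** the arm difference in change from the pre-exposure level (T2, or T1 and T2 together) to T4, in line with the training segment. T3 may be kept as an optional earlier read for the motivational mechanisms. It should not replace T4, because the post-training session also carries BASIS-T content such as public goal-setting.
- **Hypothesis 2:** decline from T4, and sustained arm differences from T4 to T6, T11 and T13. These are the last waves of the segments already defined, where group differences in level are already to be estimated.
- **T1–T2:** keep only as a pre-exposure check in which no arm difference is expected.
- State that these windows govern the primary inference, and carry the same wording into the analysis plan before outcome data are examined by arm.

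The cost is wording only. Every wave named is already collected, and no change to sample size, visits or measures is needed.

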### Randomization

This study will employ a randomized cluster-blocked cohort design with random assignment at the school level to eliminate the possibility of condition contamination among teachers. Schools will be blocked within the district by a number of teachers participating in the study, school enrollment, % of non-White students, % of students who qualify for free/reduced lunch, and mean teacher baseline BASIS-T mechanisms of change (e.g., self-efficacy). These variables were chosen because they are associated with EBPP use and student academic outcomes [59]. We will create matched pairs using the nearest neighbor approach [60] and randomly assign schools within pairs to condition. Randomization will occur to the greatest extent possible, although there may be some situations where trainers in only one condition are available when school staff are available to be trained; these situations will be considered essentially random. School personnel and participants will be masked to condition.

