#### Data analytic plan

Basic data screening and descriptives will be conducted for all quantitative variables. We will explore and statistically adjust for baseline equivalence between conditions on all individual outcomes and all school, teacher, and student variables following established guidelines [83]. For all longitudinal modeling, the statistical adjustment will use baseline intercepts as random terms; for dissimilar outcome domains, non-equivalent baseline variables will be included as covariates. Data missing at random will be modeled using full information maximum likelihood estimation or multiple imputation as appropriate.

Unless otherwise indicated, quantitative analyses will employ mixed-effects models using time points nested within classrooms within the school. Standard model-building procedures will be used [84, 85]. Classroom and time trends will be allowed to randomly vary. Piecewise time models will estimate slopes from T1 to T4 (training), T5 through T6 (first month of post-training implementation), T7–T11 (first academic year), and T12–T13 (sustainment during the subsequent year). Variables for condition and condition x time will be added, and iterative models with possible control variables will be tested. Covariates not contributing at *p* < 0.10 based on likelihood ratio tests will be removed. Level 2 and 3 predictors will be fit and excluded for the same reasons. We will obtain estimates of whether there were statistically significant differences among the groups on the rate of change over time (i.e., slope) and whether there are statistically significant group differences in the average score on each outcome variable at the final timepoint of each piecewise segment. Models will be generalized, with appropriate link functions (e.g., log-link, Poisson) applied based on distributional form (e.g., dichotomous, zero-inflation). Estimation will be fit using full maximum likelihood. Models will be assessed for possible violations of assumptions. Goodness-of-fit will be evaluated using likelihood ratios, deviance statistics, and fit criteria. The inference will be evaluated relative to *p* < 0.05. For RQs with multiple DVs, we will adjust for the false discovery rate using Benjamini and Hochberg’s procedure [86].

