#### Power

Our planned sample, including attrition, will provide sufficient power to test linear effects on teacher- and classroom school-level variables with a minimum detectable effect size (MDES) of small to medium effects, *d* = 0.37. We used PowerUp! [100] assuming clustering, final samples of 46 schools evenly randomized to condition, 6 teachers per school (after 15% attrition), school ICCs of 0.10 (consistent with our pilot data), and 13 timepoints. With the same assumptions as above, plus an assumption that 50% of the schools will be in a given moderator subgroup, our MDES for detecting any single school-level moderator variable is 0.48 and teacher-level moderator variable is 0.45. For mediator analyses, PowerUp! identifies power using the Sobel test, joint test, and Monte Carlo simulations. Across all tests, we will have a power of greater than 0.80 to detect reasonable and likely effects, based on our pilot trial and standard interpretations of effect sizes. We will detect an MDES equivalent to Cohen’s *d* = 0.60 for the treatment-mediator pathways (e.g., BASIS-T to implementation intention) which is lower than our actual obtained effect size from the pilot trial (which ranged from *d* = 0.61 to 1.16 for our primary mediators), an MDES of Pearson’s *r* = 0.3 for the mediator-outcome path (e.g., implementation intention to student behavior, a small effect), and an MDES of *d* = 0.10 for the direct path from treatment to student outcome.

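### RQ 1b tests time to PGD initiation with a Kaplan–Meier comparison that takes no account of school, the randomised unit; type I error is about 10–11% if the planning ICC of 0.10 applies

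*Protocol article*

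**What the plan says.** The Randomization section specifies "random assignment at the school level to eliminate the possibility of condition contamination among teachers" and adds: "We will create matched pairs using the nearest neighbor approach [60] and randomly assign schools within pairs to condition". The Power section assumes "final samples of 46 schools evenly randomized to condition, 6 teachers per school (after 15% attrition") and "school ICCs of 0.10 (consistent with our pilot data").

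The Data analytic plan sets a general rule: "Unless otherwise indicated, quantitative analyses will employ mixed-effects models using time points nested within classrooms within the school". Under RQ 1b it announces two tests of the behavioural implementation outcomes. The first is a mixed effects model for the proportion of teachers who adopt PGD. For the second, "Kaplan–Meier time-to-event analyses will be used to compare conditions on the number of days between training and PGD initiation". The text names no school frailty, cluster-robust variance, clustered log-rank test or stratification by pair for this comparison.

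Fidelity is to be analysed with "mixed effects models with sessions within teachers, testing for the main effects of condition".

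**The concern.** When whole schools are assigned to condition, the comparison of conditions has to be judged against variation between schools. A Kaplan–Meier comparison in its ordinary form judges it against variation between individual teachers. If teachers in one school start PGD at similar times, the standard error is too small and the test rejects too often.

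The protocol itself gives reason to expect such similarity. Training is delivered in groups, BASIS-T teachers share plans with colleagues, and the Limitations section rejects teacher-level randomisation because some mechanisms are socially influenced.

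Two things are at stake. Adoption is a named implementation outcome of a hybrid type 3 trial, and if the two adoption tests disagreed, the unclustered one would be the more prone to a false positive. The plan also adjusts research questions with several outcomes by the Benjamini–Hochberg procedure, which takes its input p-values as valid and cannot repair understated standard errors.

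**Working it through.** **Inputs.** From the Power section: 46 schools, 23 per arm; m = 6 teachers per school, so 46 × 6 = 276; school ICC 0.10 as a general planning value. From the Data analytic plan: significance at 0.05, sidedness not stated (two-sided assumed here).

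**The plan's own figure.** The standard error for a two-level cluster design is √[(4/46) × (0.10 + 0.90/6)] = √(0.08696 × 0.25) = 0.1474. At 80% power (assumed for the main effect):
- one-sided 5%: minimum detectable effect 0.373 (t, 44 df) or 0.367 (normal), matching the stated d = 0.37;
- two-sided 5% without covariates: 0.422 or 0.413. Reaching 0.37 two-sided needs inputs the article does not give, such as covariates or repeated measures.

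The sidedness does not affect this point. What matters is that the sample size counts school clustering at ICC 0.10.

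**Type I error if school is ignored.** Design effect DE = 1 + (m − 1) × ICC. Actual two-sided error = 2 × [1 − Φ(1.96/√DE)].

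| ICC | DE (m = 6) | Effective n, 276/DE | Type I error |
|---|---|---|---|
| 0.02 | 1.10 | 251 | 0.062 |
| 0.05 | 1.25 | 221 | 0.080 |
| 0.10 | 1.50 | 184 | 0.110 |
| 0.20 | 2.00 | 138 | 0.166 |

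At ICC 0.10, 1.96/√1.5 = 1.60, and 2 × [1 − Φ(1.60)] = 0.110. The unclustered standard error is 1 − 1/√1.5 = 18% too small.

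**Cluster size.** The Participants and recruitment section says "We will recruit approximately 276 teachers from 46 elementary schools in the USA", while the Power section has 6 per school after attrition. If 276 is the number before 15% attrition, 276 × 0.85/46 = 5.1 teachers per school remain; if 6 remain, about 6/0.85 ≈ 7 are recruited. At ICC 0.10, m = 5.1 gives 0.099 and m = 7 gives 0.121.

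**Check on a log-rank test.** The formula is for a difference in means, so the log-rank test was also simulated under no effect (6,000 runs, 46 × 6, ICC on a latent time scale, no pair matching). The 43% never initiating is set from the pilot: (74% + 40%)/2 = 57% adopting.

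| ICC | No censoring | 43% never initiating |
|---|---|---|
| 0 | 0.060 | 0.050 |
| 0.05 | 0.081 | 0.070 |
| 0.10 | 0.105 | 0.101 |

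The 0.060 at ICC 0 shows that these figures are good to about one percentage point. A school-level test on the same simulated data at ICC 0.10 gave 0.050–0.052.

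**Effect of pair matching.** Suppose matching removes a share x of the between-school variance (x is not given). The ratio of true to assumed variance becomes [ICC × (1 − x) + (1 − ICC)/6] ÷ (1/6). At ICC 0.10 and x = 0.5 this is (0.05 + 0.15)/0.1667 = 1.20, so the error is 2 × [1 − Φ(1.96/√1.20)] = 0.074. The ratio falls to 1 only when 1 − x = 1/6, that is, when matching removes about 83% of the between-school variance.

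**The case against.** **The test is not named.** The article never says log-rank, and a condensed article may leave the variance estimator to an analysis plan. This has some force: the document does not rule out a clustered version. But it does fix the method, presents it as a test, and moves it outside the mixed-model family that supplies school elsewhere. Followed as written, it leaves the randomised unit out.

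**The importance is limited.** This stands. The primary hypotheses are under RQ 1a and use 3-level models. The proportion adopting has its own mixed model, to which the school-nested default applies. A reader might infer that the trial's conclusion on adoption rests on an invalid test; the document does not support that.

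**The size is conditional.** This also stands. The ICC of 0.10 is not stated for time to initiation, and matching may reduce the inflation. A reader might infer that the error rate is doubled whatever the inputs; at ICC 0.02–0.05 the formula gives only 0.062–0.080.

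**Fidelity.** A reader might infer from "mixed effects models with sessions within teachers, testing for the main effects of condition" that the fidelity model drops school too. That is not established. Fidelity stays within mixed effects models, and the phrase can be read as replacing only the lowest level of the default, time points, with sessions. The adoption and reach models do not mention school either and are naturally read under that default. Any inflation figure for fidelity would also need the number of sessions and a teacher-level ICC, which the article does not give.

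**Conclusion.** Wrong as written, for time to initiation only. The Kaplan–Meier comparison departs from the school-nested default and makes no allowance for the unit of randomisation. With 6 teachers per school, an unclustered two-sided 5% test has a true type I error of about 10–11% at ICC 0.10 and about 7–8% at ICC 0.05. These figures assume that the test is an ordinary unclustered one, that an ICC in this range applies to time to initiation, and that pair matching removes little between-school variance. The direction of the error is firm unless the ICC is near zero or the matching is very effective.

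It should be fixed, but it does not threaten the trial's primary inference. For fidelity the finding is an ambiguity of wording.

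**What to change.** - **Time to initiation.** Keep Kaplan–Meier curves by condition as description. Test the difference with a Cox model, or with a discrete-time (complementary log-log) model if initiation is known only to the survey interval, with a school random effect (frailty) or cluster-robust variance. A clustered log-rank test would also do. Account for the matched pair where feasible.
- **Not recommended: a within-pair permutation test.** The Randomization section allows some schools to be assigned by trainer availability and treats this as essentially random, so the basis for such a test is doubtful.
- **Fidelity.** Confirm in one line that the model has sessions within teachers within schools.

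The cost is a change of wording and standard software, with no new data and no change in sample size. The downside is a larger standard error and p-value: at ICC 0.10 the standard error grows by √1.5 − 1 = 22%, so a result just at p = 0.05 unclustered would become about p = 0.11.
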